**Sample Size**

We identified several meta-analyses that have evaluated self-efficacy in terms of knowledge acquisition and confidence in implementing skills acquired in training programs. A 2016 Cochrane review reported a standardized mean difference effect size of 0.87 for 4 educational interventions designed to change knowledge of sickle cell disease among patients and caregivers (standardized mean difference = 1.12 with an outlier study removed).^1^ Several other similarly focused meta-analyses have reported effect sizes of between 0.58 and 0.94.^2-5^ In the SPIN-SSLED non-randomised feasibility trial, which only included 10 participants, the pre-post change in self-efficacy for carrying out leadership tasks was 1.7 standard deviations.^6^ For an assumed effect size of 0.70, a two-tailed test with α = 0.05, and an intra-class correlation coefficient (ICC) of 0.05, N = 75 would provide ≥ 80% power for self-efficacy for carrying out leader tasks. There was no loss to follow-up in our feasibility trial. Assuming 20% loss to follow-up in the proposed trial, we would need to randomise 94 support group leaders. We believe that this is a conservative power and sample size estimate. First, based on existing systematic reviews and on results of our feasibility trial, we believe that the true effect size is likely larger than 0.70. Second, in cluster RCTs, ICC values for individual patient outcomes are typically lower than our 0.05 estimate, even when different interveners are involved,^7-9^ and we will use the same trainer across groups in each language. If the true ICC is lower than our 0.05 estimate, this will result in greater power than estimated. Third, there was no loss to follow-up in our feasibility trial, and in our previous completed studies in SSc that required follow-up, loss to follow-up has been 10% or less.^10,11^

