For the secondary outcomes (emotional distress, burnout, leader satisfaction (participation efficacy)), based on published meta-analyses, a standardized mean difference effect size of 0.50 represents a clinically meaningful effect size for improvement that has been achieved in training programs for managers, caregivers of chronically ill patients, and parents of children with difficult behavior.^2,12-14^ This is also considered a clinically meaningful effect size for patient-reported health outcomes, including depressive symptoms.^15^ For effect size = 0.50, a two-tailed test with α = 0.05, and an ICC of 0.05, N = 146 would provide ≥ 80% power for both self-efficacy and patient-reported health outcomes. Assuming 20% loss to follow-up in the proposed trial, we would need to randomise 182 support group leaders. We did not estimate power for leader satisfaction.

Members of our Support Group Leader Advisory Team and our patient organization partners have emphasized the importance of evaluating the trial’s planned secondary outcomes. Thus, we will attempt to enrol 180 participants total (15 training groups of 6 participants; 90 participants in waitlist control) in order to have sufficient power to adequately evaluate secondary outcomes.

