2. Analyses of secondary outcomes will similarly be done (1) controlling for baseline scores only and (2) controlling for baseline scores and additional covariates. However, OLBI and VSI were only collected and will only be assessed among experienced leaders, since they are not relevant to candidate leaders. Thus, these analyses will not include leader experience as an additional covariate.
3. To aid in the interpretation of study results, for primary and secondary outcomes, post-intervention and 3 months post-intervention, we will produce model-adjusted standardized mean differences (Hedges’ g), using an adapted version of the method proposed by Borenstein and Hedges.^20^ For each outcome and time point, we will calculate the associated Hedges’ g estimate by dividing the unstandardized regression coefficient for the intervention effect by the unadjusted standard deviation of the outcome variable. To produce standard errors, we will use formula 11.31 from Borenstein and Hedges, which incorporates an estimate of the proportion of unexplained variance in the model (i.e., “1 - R^2^” in a standard linear regression model).^20^ In our case, we will estimate this proportion by dividing the estimated residual variance from the model by the unadjusted variance of the outcome variable. Estimated Hedges’ g and associated standard errors will be computed in each imputed dataset and then results will be pooled across imputed datasets using Rubin’s rules.^19^ Since the Borenstein and Hedges formula was not designed for the PN-RCT but was adapted, it approximates Hedges’ g and 95% CI.

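### Hedges' g is divided by an outcome SD that, read plainly, spans both arms and so contains the intervention effect; the reported g is pulled slightly toward zero

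*SAP*

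**What the plan says.** The item on Hedges' g in the SAP, under Data Preparation and Analysis, promises a model-adjusted standardized mean difference for the primary and secondary outcomes at both follow-up times, as an aid to interpretation. The estimate comes from "dividing the unstandardized regression coefficient for the intervention effect by the unadjusted standard deviation of the outcome variable". The standard error uses a formula from a cited handbook chapter, "which incorporates an estimate of the proportion of unexplained variance in the model". The plan estimates that proportion by "dividing the estimated residual variance from the model by the unadjusted variance of the outcome variable" and likens it to 1 − R² in an ordinary linear regression. Both quantities are computed in each imputed dataset and pooled with Rubin's rules. The item closes with a caveat: "Since the Borenstein and Hedges formula was not designed for the PN-RCT but was adapted, it approximates Hedges’ g and 95% CI". The amendments at the end of the SAP change the imputation and the random effects of the primary model, but not this item.

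**The concern.** A standardized mean difference expresses the difference between arms in units of the spread of individuals within an arm. The SD of a post-intervention outcome taken over both arms is larger than that whenever the intervention works, because part of the spread is the shift between the arms. The larger the effect, the larger the divisor.

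Two features of the text point to the whole-sample SD. The phrase carries no within-arm, pooled, baseline or waitlist qualifier. The next step uses the corresponding variance as the denominator of a 1 − R² analogue, and in ordinary regression that denominator is the total variance over all participants.

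At stake is the scale of a reported quantity. A reader who sees a value labelled Hedges' g will set it beside other standardized mean differences, including those in the SAP's own Sample Size section. Under the rule as written it is not quite on that scale, and the gap differs between outcomes according to the size of their effects.

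**Working it through.** **1. Plan's own figures.** The SAP states no numerical value for g. Its Sample Size section does use standardized effects, and these can be reproduced by taking them in within-arm SD units.

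- Inputs: "For an assumed effect size of 0.70, a two-tailed test with α = 0.05, and an intra-class correlation coefficient (ICC) of 0.05, N = 75" for the primary outcome; groups of 6; power of at least 80%.
- Per arm, n = 2(1.96 + 0.8416)²/0.70² = 32.04, so 33 (34 with the t distribution).
- Design effect: 1 + 5 × 0.05 = 1.25 in the intervention arm and 1 in the waitlist arm, average 1.125.
- Total: 66 × 1.125 = 74.25, or 68 × 1.125 = 76.5, against the stated 75.
- For an effect of 0.50 the same method gives 126 × 1.125 = 141.75, or 128 × 1.125 = 144, against the stated 146, which is within 3%.

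The planning effects therefore behave as ordinary within-arm standardized differences.

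**2. What the whole-sample SD contains.** Let σ be the within-arm SD, equal in both arms, d the true difference in units of σ, and p the proportion in one arm. Then

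total variance = σ² + p(1−p)d²σ² = σ²(1 + p(1−p)d²),

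reported g = dσ / [σ sqrt(1 + p(1−p)d²)] = d / sqrt(1 + p(1−p)d²).

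The Sample Size section plans 90 and 90, so p = 0.5, p(1−p) = 0.25, and the factor is 1/sqrt(1 + d²/4).

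**3. Numbers.** The effects are those named in the Sample Size section: 0.50 (secondary outcomes), 0.70 (primary) and 0.58 to 0.94 (the range from other meta-analyses).

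| True d | 1 + d²/4 | Reported g | Understatement |
| --- | --- | --- | --- |
| 0.50 | 1.0625 | 0.485 | 3.0% |
| 0.58 | 1.0841 | 0.557 | 4.0% |
| 0.70 | 1.1225 | 0.661 | 5.6% |
| 0.94 | 1.2209 | 0.851 | 9.5% |

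**4. Finite sample.** At N = 180 the whole-sample variance, in units of σ², is (178 + 45d²)/179. This gives 0.486 at d = 0.50 (2.75% low) and 0.662 at d = 0.70 (5.4% low). The usual small-sample factor for g, 1 − 3/(4 × 178 − 1) = 0.996, is not mentioned in the item. Leaving it out offsets only about 0.4 percentage points.

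**5. Simulation.** Each of 4,000 data sets per effect had 15 groups of 6 plus 90 waitlist participants, an ICC of 0.05 in the intervention arm, and a baseline-adjusted least-squares coefficient. The baseline correlation of 0.5 is an assumption. Mean g with the whole-sample SD was 0.484 for d = 0.50 and 0.660 for d = 0.70. With the pooled within-arm SD it was 0.501 and 0.703.

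**6. Unequal arms.** Since p(1−p) is largest at p = 0.5, the table shows the maximum for equal arm variances. As an illustration, p = 0.4 gives p(1−p) = 0.24. At d = 0.50 the factor is then 1/sqrt(1.06) = 0.971, an understatement of 2.9% instead of 3.0%.

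**7. Standard error.** With the whole-sample variance as denominator, the unexplained proportion is multiplied by the square of the same factor. At d = 0.70 this is 1/1.1225 = 0.891.

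**The case against.** **The wording is not explicit.** The plan never says that the SD is taken over both arms together. The word unadjusted may mean only that the SD is not the model's residual SD, and the method adapts a source that the SAP does not reproduce. This stands as a limit on certainty. But nothing in the item points to a within-arm SD, and the 1 − R² analogy points the other way. A programmer following the text would compute the SD of the whole outcome column. If a within-arm SD was meant, the SAP still needs to say so.

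**The shift is small.** Before baseline adjustment and ignoring clustering, the standard error of g at N = 180 is about sqrt(4/180 + g²/360), or roughly 0.15. The shifts of 0.015 at d = 0.50 and 0.039 at d = 0.70 are about 10% and 25% of that. Baseline adjustment would raise these ratios somewhat, but both shifts stay well below one standard error. The distortion is also toward zero, so it cannot inflate the apparent benefit. This stands, and it is why the point is minor.

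**The plan already calls g approximate.** It does, but the reason it gives is the adaptation to the partially nested design. The choice of standardizer would produce the same distortion in any two-arm trial, so the caveat does not tell the reader about it.

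**The interval may be little harmed.** If the residual part of the standard error is proportional to the square root of the unexplained proportion, it shrinks by the same factor as g, and their ratio is largely preserved. The cited formula is not given in the SAP, so the net effect on the interval is not quantified here. A reader might infer that the interval is materially wrong; the document does not show that.

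**A benchmark reading.** A reader might also infer that g will be judged against 0.50 or 0.70. The Sample Size section does call 0.50 clinically meaningful, but both values enter as planning inputs. The SAP attaches no success rule, test or decision to g.

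**Conclusion.** On its plain reading, the rule understates g by the factor 1/sqrt(1 + p(1−p)d²): about 3% at 0.50, 6% at 0.70 and 9.5% at 0.94. These figures assume that the SD is taken over all participants, that the arm variances are equal and, for the percentages, that allocation is 1:1. OLBI and VSI are analysed only in experienced leaders, where 1:1 balance is not assured; with equal variances, imbalance makes the understatement slightly smaller.

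The effect is confined to the interpretive g and its confidence interval. The unstandardized intervention coefficient from the mixed model and its test do not use this SD.

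A reader might infer a far larger distortion from the feasibility result, where "the pre-post change in self-efficacy for carrying out leadership tasks was 1.7 standard deviations". That figure is a change over time in 10 participants of a non-randomised study. It is not a difference between arms and has no place as d in this formula.

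The point is a real but minor correction to how a reported quantity is defined.

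**What to change.** State that g is the intervention coefficient divided by the pooled within-arm SD of the unadjusted outcome at that time point, computed in each imputed dataset:

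sqrt{[(n₁ − 1)s₁² + (n₂ − 1)s₂²] / (n₁ + n₂ − 2)},

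where s₁ and s₂ are the SDs in the two arms and n₁ and n₂ the numbers analysed for that outcome. Use the square of this SD as the denominator of the unexplained-variance term in the standard error, so that g and its interval are on one scale. Changing the divisor of g alone would leave the two on different scales.

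The cost is a phrase in the SAP and about one line of code. No new data are needed, and the primary model and the imputation are unchanged.

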1. Trial outcomes will be assessed pre-randomisation, immediately following the 13-week intervention, and 3 months after the end of the intervention period for both participants randomised to the intervention and participants randomised to waitlist.

All analyses will be conducted in R, and will be 2-sided, using an alpha value of 0.05. There will be no adjustment for the multiplicity of secondary outcomes.

For the primary outcome analysis (SGLSS post-intervention), we will use an intent-to-treat analysis that compares all participants randomly assigned to the SPIN-SSLED Program to all participants randomly assigned to the waitlist control. The intervention effect immediately post-intervention will be estimated using a linear mixed-effects model (using the lmer function in lme4),^16^ including baseline SGLSS scores as a fixed effect. To account for the clustering inherent to the blocked PN-RCT design, we will fit a random intercept and slope for intervention by randomisation block and an additional random slope for intervention-by-intervention cluster (i.e., participants in the intervention arm who were in a trial group with the same group leader).^17^

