**Amendments to Statistical Analaysis Plan**

1. The mice procedure needed to be modified to run successfully. We removed randomisation block, intervention arm, whether the leader has SSc, and whether the leader is an experienced versus candidate leader from the list of variables included in the mice procedure, as these variables were collinear with other variables included in the mice procedure. We also did not use the ‘where’ option to account for non-applicable responses, as this was not possible after removing these variables from the mice procedure. Instead, we re-set non-applicable values to ‘NA’ after the mice procedure was completed.
2. For the primary outcome (SGLSS scores immediately post-intervention), the intended analytical models did not converge. Thus, these analysis models were simplified to remove random slopes and to only include a single random intercept for each separate intervention group and for all waitlist participants combined (i.e., not separated by randomisation block) to facilitate convergence.

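### The standard error and 95% CI of Hedges' g leave out the training-group variance, so the interval for g is too narrow (about 7% at the SAP's ICC)

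*SAP*

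**What the plan says.** In the SAP's Data Preparation and Analysis section, the primary analysis is a linear mixed model. "To account for the clustering inherent to the blocked PN-RCT design", the plan states, "we will fit a random intercept and slope for intervention by randomisation block and an additional random slope for intervention-by-intervention cluster". Estimates are pooled over imputed datasets with Rubin's rules.

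A later item in the same section covers standardized mean differences for every primary and secondary outcome at both follow-up times. The point estimate comes from "dividing the unstandardized regression coefficient for the intervention effect by the unadjusted standard deviation of the outcome variable". For the standard error, "we will use formula 11.31 from Borenstein and Hedges, which incorporates an estimate of the proportion of unexplained variance in the model". That proportion is then defined: "we will estimate this proportion by dividing the estimated residual variance from the model by the unadjusted variance of the outcome variable". The item closes with a caveat: "Since the Borenstein and Hedges formula was not designed for the PN-RCT but was adapted, it approximates Hedges’ g and 95% CI".

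Item 2 of the amendments section simplifies the random effects for the primary outcome, so that those models "only include a single random intercept for each separate intervention group and for all waitlist participants combined". It leaves the g calculation unchanged.

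**The concern.** In ordinary regression, 1 − R² is the share of outcome variance that covariates leave unexplained, and all of it feeds the uncertainty of the arm contrast. A mixed model splits the unexplained variance into residual variance and random-effect variances. Putting only the residual part into the formula treats differences between training groups as if a covariate had removed them.

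They have not been removed. In a partially nested design the training groups exist only in the intervention arm, so their variance passes straight into the difference between arms. The step also moves the wrong way: the more group variance the model finds, the smaller the residual variance and the smaller the stated SE of g.

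The SAP expresses its sample size in standardized units (0.70 and 0.50), so readers are likely to judge the results on g and its interval. That interval can also disagree about zero with the interval for the unstandardised coefficient in the same analysis.

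**Working it through.** **Inputs from the SAP (Sample Size).** ICC 0.05; 15 training groups of 6 (90 people) against 90 unclustered waitlist participants; two-sided alpha 0.05; effect sizes 0.70 and 0.50; 20% loss to follow-up.

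**Assumptions.** The algebra of formula 11.31 is not printed in the SAP. I take it as SE = sqrt[ q·(n1+n2)/(n1·n2) + g²/(2(n1+n2)) ], where q is residual variance over outcome variance. ICCs other than 0.05 are assumed, to show the range.

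**Step 1: does the design count clustering?** The SAP states no SE for g, so the sample size is the figure to reproduce. Per arm, n = 2(1.96 + 0.84)²/d², which gives 33 for d = 0.70 and 63 for d = 0.50. The design effect is 1 + (6 − 1) × 0.05 = 1.25 in the intervention arm and 1 in the waitlist arm, a mean of 1.125.

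- d = 0.70: 66 × 1.125 = 74.25, so 75. The SAP states 75.
- d = 0.50: 126 × 1.125 = 141.75, so 142 (144 with a t-based n). The SAP states 146, within 3%.

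The sample size therefore does allow for clustering in the intervention arm. The SE of g does not.

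**Step 2: the two variances.** Scale the intervention-arm variance to 1, so that group variance = ICC and residual variance = 1 − ICC in both arms. Take g = 0 and no baseline adjustment.

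- As the SAP describes it: (1 − ICC) × 2/90.
- With the group variance: ICC/15 + (1 − ICC) × 2/90.

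At ICC 0.05:

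- As described: 0.95 × 2/90 = 0.02111, SE 0.145.
- With group variance: 0.05/15 + 0.02111 = 0.02444, SE 0.156.
- Ratio: sqrt(0.02111/0.02444) = 0.929, so the SE is 7% too small.
- Coverage: 2Φ(1.96 × 0.929) − 1 = 93.1%.

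| ICC | SE as described | SE with group variance | Shortfall | Coverage |
|---|---|---|---|---|
| 0.01 (assumed) | 0.148 | 0.151 | 1.5% | 94.65% |
| 0.02 (assumed) | 0.148 | 0.152 | 3% | 94.3% |
| 0.05 (SAP) | 0.145 | 0.156 | 7% | 93.1% |
| 0.10 (assumed) | 0.141 | 0.163 | 13% | 91.0% |
| 0.20 (assumed) | 0.133 | 0.176 | 24% | 86.2% |

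**Step 3: sensitivity.**

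- If baseline explains half the variance and g = 0.50, the SEs at ICC 0.05 are 0.106 and 0.114.
- With 20% lost (72 per arm) and otherwise the same inputs, they are 0.119 and 0.125.
- If the waitlist arm is given the full unexplained variance rather than the residual part only, the shortfall at ICC 0.05 (g = 0) is about 8% and coverage is 92.8%.

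**Step 4: comparison with simply ignoring clusters.** At ICC 0.05, g = 0 and half the variance explained, an SE that ignores clustering but keeps all unexplained variance is 0.105. The SAP's is 0.103. With clustering it is 0.111 to 0.112.

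**Step 5: simulation.** There were 20,000 runs with half the variance explained, g = 0 and the outcome SD taken as known. The described interval covered 92.8%, 91.0% and 85.6% at ICC 0.05, 0.10 and 0.20. An interval built from the model's variance components covered 94.8%, 94.5% and 93.7%.

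**The case against.** The strongest defence is that g is an interpretive aid and that the SAP says openly its formula was adapted to a design it was not made for. Tests at alpha 0.05 come from the mixed model, not from g. That stands, and it limits the importance of the point. It does not remove it: the caveat gives neither the direction nor the size of the error, and Rubin's rules add uncertainty for missing data, not for groups.

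The size is also modest on the plan's own terms. The Sample Size section expects ICCs below 0.05, where coverage lies between about 93% and 95%. The burnout and satisfaction outcomes cover experienced leaders only, so their clusters are smaller and the shortfall is smaller still. At ICC 0.05 the two intervals disagree about zero only when |z| falls between about 1.82 and 1.96, roughly 2% of the time under the null.

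Nor is every random-effect variance wrongly dropped. In the planned model the block intercept is shared by both arms and largely cancels from the contrast, so leaving it out is right. The complaint concerns the intervention-slope and training-group variance.

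A reader might set the SE of g against the SE from the amended primary model, sqrt(0.05/15 + 0.05 + 0.02111) = 0.273, and infer that the SE of g is only 53% of what it should be. The documents do not support that. The extra 0.05 comes from giving the whole waitlist one shared random intercept. That is a separate problem, it inflates the model's SE, and it concerns one of the eight outcome-by-time analyses. The proper comparison is 0.145 with 0.156.

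**Conclusion.** The point holds for the SE and 95% CI of Hedges' g. A reader might infer that all the trial's reported intervals ignore clustering; they do not. Intervals for the unstandardised effects come from the mixed model, and the point estimate of g uses that model's coefficient.

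At the SAP's ICC and planned group sizes, the SE of g is about 7% too small and a nominal 95% interval covers about 93%. The shortfall is trivial at an ICC of 0.01 and serious only at values such as 0.20, which are assumptions and higher than the SAP expects. The exact figures rest on the assumed form of formula 11.31. The direction needs only what the SAP states: the formula uses 1 − R², was not made for this design, and receives residual variance alone. This should be corrected, but it does not touch the primary test.

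**What to change.** In each imputed dataset, compute SE(g) as the model's SE of the arm coefficient divided by the same SD that standardizes g, adding the small term for estimating that SD if wanted. Pool with Rubin's rules as planned, and drop the residual-variance substitution for 1 − R².

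The SAP must name the model that supplies the SE: a partially nested model with a training-group random effect in the intervention arm only and no random intercept shared by the whole waitlist. The amended primary model as written should not be used, since at ICC 0.05 it would move the SE from 0.145 to 0.273 rather than to 0.156.

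The cost is a few lines of code, a short change of wording, and slightly wider intervals for g. No new data are needed. If the present method is kept, the SAP should at least say that its intervals for g omit training-group variance and so tend to be too narrow.
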